### 7.2.2 Cellular immunogenicity

MVA-specific T-cell responses will be monitored in a subgroup of 50 subjects from Group 1 (healthy) and 110 subjects from Group 2 (AD) with samples taken at each of the Visits 1, 2 and 4 collected at US sites by measurement of IFN- $\gamma$  production after stimulation with MVA-BN using an IFN- $\gamma$  ELISPOT assay. A MVA-specific response is defined by a frequency of at least 50 SFU (spot forming units) /  $10^6$  cells after correction for background (SFU /  $10^6$  non-stimulated cells).

The immune cell analyses will be performed at BN's laboratory at Bavarian Nordic GmbH, [name].

## 8. Adverse event definitions and reporting

Any change in health observed before first vaccination will be recorded in the “baseline signs and symptoms” section of the CRF and will not be considered an adverse event.

### 8.1 Definition of adverse event

Adverse events are defined as any untoward (undesirable) medical occurrence in a clinical trial subject administered a medicinal product and which does not necessarily have a causal relationship with this medication. All adverse events (e.g. feeling of ill-health, subjective symptoms and objective signs, intercurrent diseases, accidents, etc.) observed by the Investigator and/or reported by the subject must be recorded in the CRF regardless of the assessment of causality in relationship with the study drug.

Abnormal laboratory values that were assessed as clinically significant by the Investigator are to be documented as AEs. In addition, abnormal laboratory values fulfilling the Grade 3 criterion according to the toxicity scale (Appendix I) are to be documented as AEs, regardless of whether they are considered clinically relevant or not.

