### 8.4 Definition of “adverse event of special interest”

An “adverse event of special interest” is defined in this study as an adverse event fulfilling any of the following features:

- Any cardiac symptom
- ECG changes, which are determined to be clinically significant
- Cardiac enzymes elevated above ULN

Adverse events of special interest are to be reported according to the procedures and timelines applicable for serious adverse events.

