| Cardiac Troponin I                           | >ULN – <2.0 x
ULN        | $\geq 2.0$ - < 5.0 x
ULN | $\geq 5.0$ x ULN      |                                              |
| Total Cholesterol
mg/dL                   | > ULN - 300                 | > 300 - 400                 | > 400                 |                                              |

| HEMATOLOGY                                                           |                        |                           |                     |                                              |
|----------------------------------------------------------------------|------------------------|---------------------------|---------------------|----------------------------------------------|
| Lab Value                                                            | Mild
(Grade 1)      | Moderate
(Grade 2)     | Severe
(Grade 3) | Potentially Life
Threatening
(Grade 4) |
| Hemoglobin (Female) - g/dl                                           | < LLN - $\geq$ 10.5    | < 10.5 - $\geq$ 10.0      | < 10.0              |                                              |
| Hemoglobin (Male) - g/dl                                             | < LLN - $\geq$ 12.0    | < 12.0 - $\geq$ 11.0      | < 11.0              |                                              |
| WBC Increase - cell/mm                                   | $\geq$ ULN - < 15,000  | $\geq$ 15,000 - < 20,000  | $\geq$ 20,000       |                                              |
| WBC Decrease - cell/mm                                   | < LLN - $\geq$ 2,500   | < 2,500 - $\geq$ 1,500    | < 1,500             |                                              |
| Lymphocytes Decrease - cell/mm                           | < 1,000 - $\geq$ 750   | < 750 - $\geq$ 500        | < 500               |                                              |
| Neutrophils Decrease - cell/mm                           | < 2,000 - $\geq$ 1,500 | < 1,500 - $\geq$ 1,000    | < 1,000             |                                              |
| Platelets Decreased - cell/mm                            | < LLN - $\geq$ 100,000 | < 100,000 - $\geq$ 75,000 | < 75,000            |                                              |

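### Sections 8.1 and 8.4 conflict on whether a troponin I above 1 and below 5 x ULN is an adverse event of special interest

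*Protocol*

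**What the plan says.** Section 8.1 first gives a general definition: "Adverse events are defined as any untoward (undesirable) medical occurrence in a clinical trial subject administered a medicinal product". For laboratory results it then names two cases that must be recorded. The first rests on judgement: "Abnormal laboratory values that were assessed as clinically significant by the Investigator are to be documented as AEs". The second does not: "abnormal laboratory values fulfilling the Grade 3 criterion according to the toxicity scale (Appendix I) are to be documented as AEs", whether or not they are thought clinically relevant.

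Section 8.4 says that an event of special interest "is defined in this study as an adverse event fulfilling any of the following features". The three features are:

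- "Any cardiac symptom"
- "ECG changes, which are determined to be clinically significant"
- "Cardiac enzymes elevated above ULN"

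Only the ECG feature carries a condition of clinical significance.

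The row "Cardiac Troponin I" in Appendix I grades values above ULN and below 2.0 x ULN as Grade 1, from 2.0 to below 5.0 x ULN as Grade 2, and from 5.0 x ULN as Grade 3. It has no Grade 4.

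Special-interest events go to the CRO safety department within 24 hours (section 8.6). Section 9.4.3 lists and tabulates them and compares their incidence between the groups by Fisher's exact test or chi-squared.

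**The concern.** The enzyme threshold in 8.4 is ULN, but it applies to an adverse event, and the only automatic laboratory route to that status in 8.1 starts five times higher. One site can read 8.1 first and leave out a troponin I of, say, 3 x ULN that it considers not clinically significant. Another can read 8.4 first and report the same value. The two sites then produce different special-interest counts from identical laboratory results.

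The trial is open-label and its groups are defined by disease, so whoever judges significance knows the subject's group. Where the judgement decides, the Fisher comparison could partly reflect recording practice instead of a difference between subjects with atopic dermatitis and healthy subjects. Troponin I is measured at a central laboratory, so this dependence on judgement is avoidable.

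**Working it through.** The protocol states no figure on this point, so there is none to reproduce. The check is a comparison of the sections, followed by an illustration.

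**Inputs.** AE rules for laboratory values: 8.1. Special-interest features: 8.4. Troponin grades: Appendix I. Scheduled troponin I: screening, Visit 2 and Visit 4 (7.1.3), with Visit 5 and F-U only if clinically indicated. Subjects: 560 (4.1), as 230 healthy and 330 with atopic dermatitis (Appendix V). Entry limit: troponin I below 2 x ULN (4.2, criterion 7). Changes seen before first vaccination are not AEs (opening of section 8).

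**Step 1: the rules side by side**, for a subject with no cardiac symptom and no significant ECG change.

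| Troponin I | Must be an AE under 8.1? | Meets 8.4 feature? | Special interest, AE status first | Special interest, 8.4 prevails |
|---|---|---|---|---|
| Grade 1 (>1 to <2 x ULN) | Only if judged significant | Yes | By judgement | Always |
| Grade 2 (2 to <5 x ULN) | Only if judged significant | Yes | By judgement | Always |
| Grade 3 (5 x ULN or more) | Yes | Yes | Always | Always |

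The two readings differ over all of Grades 1 and 2 and nowhere else.

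**Step 2: does the text decide?**

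- For AE status first: 8.4 speaks of an adverse event that has a feature. The express rule for Grade 3 in 8.1 would be unnecessary if every abnormal value were already an AE. Section 7.1.4 has the investigator rate an adverse event as one of special interest, and then points to a section 8.7, although the table of contents ends section 8 at 8.6.
- For 8.4 prevailing: 8.1 does not say that other values are not AEs. The enzyme feature omits the significance condition that the ECG feature has.

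Neither reading is excluded, and no text gives an order of precedence.

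**Step 3: how many results.** Scheduled post-vaccination tests number at most 560 x 2 = 1,120. The protocol gives no rate above ULN. Assuming 0.5% to 2%, 1,120 x 0.005 = 5.6 and 1,120 x 0.02 = 22.4, so about 6 to 22 results. These are test results, whereas Fisher's test counts subjects. Some of the results could also be Grade 3 and outside the dispute.

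**Step 4: effect on the Fisher comparison.** This is an illustration with assumed rates. True rates are identical in both groups: other special-interest events 1% or 3%, troponin I above 1 and below 5 x ULN 1%, 2% or 5%. The recorded rate in a group is the other rate plus the troponin rate times the share recorded. The rejection probability of the two-sided 0.05 test was enumerated exactly for 230 against 330.

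| Share recorded, Group 1 / Group 2 | Rejection rate over the assumed range |
|---|---|
| Equal (0/0, 50%/50%, 100%/100%) | 2.5% to 4.2% |
| 20% / 80% | 4.4% to 42.4% |
| 0% / 100% | 7.4% to 90.4% |

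One case in full, with other events 1% and troponin 2%. Full recording gives 230 x 0.03 = 6.9 and 330 x 0.03 = 9.9 expected subjects, and rejection in 3.7%. Recording of 20% and 80% gives 230 x (0.01 + 0.02 x 0.2) = 3.2 and 330 x (0.01 + 0.02 x 0.8) = 8.6, and rejection in 10.8%.

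**Step 5: values already raised at entry.** Criterion 7 lets a subject enter with troponin I above ULN but below 2 x ULN. An unchanged value at Visit 2 meets the 8.4 feature, although the elevation pre-dates vaccination. Neither 8.1 nor 8.4 says how to count it.

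**The case against.** The strongest answer is that this is a missing cross-reference. Section 8.1 sets minimum recording duties and never uses the word only; its general definition also covers objective signs. Section 8.4 is the more specific rule and its authors left significance out of the enzyme feature, so the natural reading may be that every value above ULN counts. This is a fair reading, but the text does not compel it.

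Several wider inferences are tempting, and the documents do not support them:

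- **That the whole cardiac comparison rests on opinion.** The symptom feature has no significance condition, the ECG feature has its own wording and ECGs are evaluated centrally, and troponin I from 5 x ULN is an AE automatically.
- **That low-level elevations vanish from the trial.** Section 9.4.3 counts laboratory values outside the reference range whatever their AE status. At most they are absent from the special-interest table.
- **That the comparison is biased.** Equal under-recording does not inflate the error rate, and nothing shows that recording differs by group.
- **That 24-hour reporting certainly fails.** A note in 7.1.9 starts the cardiac algorithm at any scheduled troponin abnormality. That chart and the reporting chart in 8.6 are figures that could not be read here, and either might bear on the question.

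Nor is the special-interest comparison among the endpoints in 9.2.2, and section 9.3 ties confirmatory testing to humoral immunogenicity. All of this limits the consequences. It does not settle which section governs Grade 1 and Grade 2 values.

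A last objection concerns the remedy: making every post-vaccination value above ULN a special-interest event would sweep in unchanged elevations from screening. That is right, and the fix has to address it.

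**Conclusion.** The point stands in a limited form. Sections 8.1 and 8.4 give two defensible and different special-interest counts for asymptomatic troponin I above 1 and below 5 x ULN, and the protocol text does not choose between them. On one reading an unblinded investigator's judgement decides whether such a value enters the listing, the 24-hour reporting and the Fisher comparison; on the other it always enters.

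The size cannot be taken from the protocol. The 6 to 22 results rest on an assumed rate of 0.5% to 2% and the maximum of 1,120 tests. The rejection rates rest on assumed event rates and, for any inflation, on recording that differs by group. The open-label design permits that difference, but the documents do not show it. The primary immunogenicity analysis is untouched.

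**What to change.** 1. Add a cross-reference in 8.1 that states which rule governs cardiac enzymes above ULN, so that 8.1 and 8.4 give one answer for Grade 1 and Grade 2 troponin I. Which rule that should be is for the sponsor to settle. Correct the reference to section 8.7 in 7.1.4 at the same time.
2. State how values already above ULN at screening are treated, given criterion 7 and the rule in section 8 on changes before first vaccination.
3. In 9.4.3, derive the troponin component of the special-interest comparison per subject from the central-laboratory data for all vaccinated subjects. Separate new or increased elevations from those present at screening.

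The cost is a short text change, one extra derivation from data already collected and possibly a few more special-interest records. If sites have already finished recording, the text change cannot alter what they entered, but the derivation still gives a count that does not depend on judgement.

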## 5. Study halting/termination and withdrawal of subjects

### 5.1 Study halting and termination rule

A temporary halting or termination for single study subjects or for the study as a whole can be decided in case of an occurrence of

- a serious adverse event (SAE)
- an unexpected grade 3 or higher systemic reaction or lab toxicity

with an at least reasonable possibility of a causal relationship to the administration of MVA-BN® (IMVAMUNE®), i.e. the relationship cannot be ruled out.

These parameters are not all-inclusive. Other adverse events could occur that would trigger a Data Safety Monitoring Board (DSMB) review. Any member of the DSMB, the Principal Investigator, BN Safety Officer, or DMID Medical Officer could request a Safety Monitoring Committee review based on any observation.

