#### **7.1.3 Laboratory measurements**

The intensity of laboratory / systemic quantitatively measured toxicities will be graded according to the toxicity scale in Appendix I. These grading scales include the laboratory values determined with the routine safety parameters. In case of other laboratory values not included in the routine safety laboratory and not listed in Appendix I, the National Cancer Institute (NCI) Common Toxicity Criteria table, Version 2.0, published April 30, 1999 will be used for grading of laboratory toxicities.

SAFETY LABORATORY:

Safety laboratory is determined at the screening visit (Visit SCR) and 7 – 14 days after each vaccination (for Visit 2: 7-10 days and Visit 4: V3+10-14 days). At Visit 5 and at follow-up visit (Visit F-U) safety laboratory is only done if clinically indicated. The safety laboratory measurements are performed at the central laboratory. Laboratory normal ranges are provided by the central laboratory and filed in the Investigator file. Safety laboratory parameters to be evaluated are:

Hematology:

Red blood cell count, hemoglobin, total and differential WBC, platelet count..

Serum chemistry:

Total bilirubin, alkaline phosphatase, AST, ALT, serum creatinine, sodium, potassium, calcium, troponin I.

PREGNANCY TEST:

$\beta$ -HCG pregnancy test will be conducted for all women with reproductive potential at screening (Visit SCR), within 24 hours prior to each vaccination (Visits 1 and 3) and at Visit 5. At screening, a serum  $\beta$ -HCG pregnancy test will be conducted, all other pregnancy test will be conducted as urine  $\beta$ -HCG test.

The following parameters will only be evaluated during the screening period (Visit SCR) for check of inclusion / exclusion criteria:

CHOLESTEROL:

Total, HDL and LDL.

URINE ANALYSIS (E.G. WITH COMBUR-10 STICK):

Protein, glucose, occult blood, nitrites, leucocytes, pH, bilirubin, ketones, urobilinogen, specific gravity.

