### 9.2.2 Safety and reactogenicity endpoints

#### Secondary endpoints

- Occurrence of any grade 3 adverse event probably, possibly or definitely related to the study vaccine within 28 days after vaccination.
- Occurrence, relationship and intensity of any serious adverse event at any time during the study.
- Occurrence of solicited local adverse events (redness, swelling and pain) within 1 week after each vaccination (Days 0-7): Intensity, duration, and relationship to vaccination.
- Occurrence of solicited systemic adverse events (redness, swelling and pain) within 1 week after each vaccination (Days 0-7): Intensity, duration, and relationship to vaccination.
- Occurrence of unsolicited non-serious adverse events within 4 weeks after each vaccination (Days 0-28): Intensity, duration and relationship to vaccination.

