#### Unsolicited adverse events:

Unsolicited adverse events will be coded with the MedDRA coding terminology. The intensity of adverse events will be graded according to section 7.1.7.

The number of adverse events and number of patients with at least one adverse event for each preferred term will be descriptively compared between treatment groups.

The occurrence of any grade 3 or higher adverse reaction probably, possibly or definitely related to the study vaccine within 28 days after vaccination will be compared between treatment groups.

The occurrence, relationship and intensity of *adverse events of special interest* at any time during the study will be separately listed and tabulated. The incidence of such AEs will be compared between treatment groups by means of the exact test of Fisher (or its normal approximation, the chi-squared test).

*Serious adverse events* will be listed separately. Each SAE will be described individually in detail. The number of subjects with at least one SAE will be compared between treatment groups by means of the exact test of Fisher (or its normal approximation, the chi-squared test).

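### Appendix I gives no grade to calcium 1.5 to <2.0 mmol/L or sodium 129 to <130 mmol/L, so the automatic laboratory adverse-event rule cannot be applied there

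*Protocol*

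**What the plan says.** Section 7.1.3 makes Appendix I the grading scale for laboratory values: "toxicities will be graded according to the toxicity scale in Appendix I". The routine chemistry panel includes "serum creatinine, sodium, potassium, calcium, troponin I", measured at screening, Visit 2 and Visit 4. Section 7.1.3 sends only parameters outside the routine panel and outside Appendix I to another published scale. Sodium and calcium are in both, so that fallback does not cover them.

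Section 8.1 gives two routes by which a laboratory value becomes an adverse event:

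- By judgement: "Abnormal laboratory values that were assessed as clinically significant by the Investigator are to be documented as AEs".
- Automatically: "abnormal laboratory values fulfilling the Grade 3 criterion according to the toxicity scale (Appendix I) are to be documented as AEs", regardless of clinical relevance.

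Section 5.1 lists, among the events that may lead to halting, "an unexpected grade 3 or higher systemic reaction or lab toxicity" with a reasonable possibility of a causal link to the vaccine. Section 9.2.2 has the endpoint "Occurrence of any grade 3 adverse event probably, possibly or definitely related to the study vaccine within 28 days after vaccination", and section 9.4.3 compares it between groups in a wider form: "The occurrence of any grade 3 or higher adverse reaction probably, possibly or definitely related to the study vaccine within 28 days".

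**The concern.** A rule tied to a grade works only if each abnormal value falls in exactly one grade. In the low-calcium row of Appendix I, the printed upper limit of Grade 2, and that of Grade 3, is smaller than the printed lower limit. In the low-sodium row, Grade 2 stops at 130 and Grade 3 starts below 129.

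If these cells are as the sponsor intended them to be used, the automatic route in 8.1 fails for part of two scheduled safety parameters. Whether such a value becomes an adverse event would then depend on the investigator alone, in an open-label trial that compares the two groups on safety. The same values would have no Appendix I grade when someone asks whether the laboratory-toxicity criterion in 5.1 has been met.

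**Working it through.** **Inputs.** The bands are those printed in Appendix I, in mmol/L, each read as the joint condition x < upper limit and x ≥ lower limit. The lower limit of normal (LLN) is not given in the protocol. It affects only the upper edge of Grade 1 and none of the results below. The plan states no figure to reproduce here.

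**Step 1: calcium as printed.**

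| Grade | Condition | Values that meet it |
|---|---|---|
| 1 | x < LLN and x ≥ 2.0 | 2.0 to <LLN |
| 2 | x < 1.75 and x ≥ 2.0 | none, since 1.75 < 2.0 |
| 3 | x < 1.6 and x ≥ 1.75 | none, since 1.6 < 1.75 |
| 4 | x < 1.5 | all below 1.5 |

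Grade 1 ends at 2.0 and Grade 4 starts below 1.5, so the whole interval 1.5 to <2.0 is ungraded. In steps of 0.01 this is 1.50 to 1.99, and all 50 of these values return no grade.

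**Step 2: calcium with the limits swapped within each cell.** This is the most lenient reading.

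- Grade 2 becomes 1.75 to <2.0 (25 steps of 0.01).
- Grade 3 becomes 1.6 to <1.75 (15 steps).
- Grade 4 stays below 1.5.
- Left over: 1.5 to <1.6 (10 steps; 25 + 15 + 10 = 50).

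Assuming a simple transposition therefore does not close the row, because Grade 3 would end at 1.6 while Grade 4 starts below 1.5.

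**Step 3: sodium as printed.** Grade 2 is 130 to <132, Grade 3 is 125 to <129, and Grade 4 is below 125. In whole numbers, 130 and 131 are Grade 2, 129 has no grade, 125 to 128 are Grade 3, and 124 is Grade 4. To one decimal, all of 129.0 to 129.9 is ungraded.

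**Step 4: comparison rows.** The Grade 2 to Grade 4 bands for hypernatremia, hyperkalemia, hypokalemia and hypercalcaemia in the same table run in order and meet without gaps (for example, hypokalemia 3.4 to <3.5, 3.2 to <3.4, <3.2). The faults in the two low-value rows are therefore not a general convention of the table.

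**Step 5: what each rule does with an ungraded value.**

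| Rule | Calcium 1.5 to <2.0, sodium 129 to <130 |
|---|---|
| 8.1, automatic route | cannot be applied |
| 8.1, judgement route | still available |
| 5.1, laboratory-toxicity criterion | no Appendix I grade to test |
| 9.4.3, count of out-of-range values | still counted |
| 9.4.3, comparison of related events of Grade 3 or higher | possible only if recorded and graded under 7.1.7 |

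**Step 6: scale.** With 560 planned subjects and scheduled tests at Visits 2 and 4, the rule covers 560 × 2 = 1,120 planned post-vaccination results per analyte. That is the number of tests, not the number affected. The protocol gives no expected frequency of values in the ungraded ranges.

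**The case against.** The other side accepts the reversed cells and the sodium gap but says that little follows from them. A reader might infer that severe values go unrecorded and drop out of the halting rule and the Grade 3 comparison. The protocol does not support that, for these reasons:

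- **Recording.** The judgement route in 8.1 needs no grade, and 9.4.3 counts every result outside the reference range. Only automatic recording fails.
- **Grade 3 comparison.** Section 9.4.3 grades the intensity of adverse events by the clinical scale in 7.1.7, not by Appendix I. A low calcium or sodium value recorded as clinically significant can still be Grade 3 there.
- **Halting.** The criterion covers Grade 3 and above, so calcium <1.5 (Grade 4) meets its grade condition. It also requires an unexpected event with possible causality, the decision is discretionary, and the list is open: "These parameters are not all-inclusive. Other adverse events could occur that would trigger a Data Safety Monitoring Board (DSMB) review".
- **Severity.** Nothing shows that sodium 129 is severe. It lies between two grades. On the swapped reading, half of the ungraded calcium range (1.75 to <2.0) would be Grade 2.
- **Reach of the rule.** That the automatic rule can never apply to any low calcium value is true only if the words about Grade 3 in 8.1 exclude Grade 4. The text does not settle this.
- **Purpose.** No passage says why the automatic rule was written.

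All of this stands and limits the consequences. None of it supplies the missing grades: the automatic route still cannot be applied in the two ranges, and the laboratory criterion in 5.1 still lacks an Appendix I grade to test.

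**Conclusion.** The point holds as a defect of two operative rows in Appendix I. Calcium 1.5 to <2.0 mmol/L is ungraded as printed, and 1.5 to <1.6 is ungraded even with the limits swapped. Sodium 129 to <130 mmol/L is ungraded on any reading of the printed limits. In these ranges the automatic rule in 8.1 cannot work, and whether a value becomes an adverse event depends on the investigator's judgement of clinical significance.

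The conclusion assumes that the cells are printed as the sponsor wrote them and that a band means both of its limits apply. The effect on results cannot be sized: the number of values in these ranges is unknown, may be small and could be zero. The primary ELISA analysis is not touched. The correction is worth making because these thresholds decide what is recorded and because the repair is small.

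**What to change.** The sponsor should reconcile the hypocalcaemia and hyponatremia rows of Appendix I with its source scale, so that the limits in each cell run in order, adjacent bands meet, and every value below LLN has exactly one grade. The limits are for the sponsor to confirm; none is proposed here. The stored central-laboratory calcium and sodium results should then be re-graded by program, and sections 8.1 and 5.1 applied to the re-graded values.

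The cost is the correction of two appendix rows and one programming step, with no new subjects or samples. The work may not end there. If re-grading identifies new adverse events, each needs a causality assessment by the investigator, because both the halting criterion and the comparison of related events in 9.4.3 depend on relatedness, which a program cannot supply.
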